### Statistical analysis

The demographic and clinical characteristics of the participants (center, gender, age, Venham score 0–2/3–5, vigilant state/conscious sedation) and tooth pair (maxillary/mandibular molar pair, carious lesion/hypoplastic defect, two or more surfaces affected, with or without pulpotomy) will be described using mean and standard deviation (SD) for quantitative variables and percentages for qualitative variables.

Furthermore, bivariate analysis will be used to compare the baseline characteristics between groups (e.g., left/right molars, presence or absence of a restoration with a dental material on the antagonist tooth).

An intent-to-treat (ITT) analysis will be conducted. To assess the equivalent effectiveness of ZCs, we will use a multivariable Cox hazards regression model with shared frailty including success as the dependent variable (primary outcome defined by the absence of major failure: no = 0, yes = 1), and the treatment group variable as an independent variable. This analysis will also include the potential confounders age, gender, type of tooth (i.e., first or second primary molar), pulpotomy, number of surfaces affected by the lesion, and presence or absence of a restoration with a dental material of the antagonist tooth. Cox proportional hazards models, using the PHREG procedure will estimate the HR and the 95% CI. In these analyses, a random statement will be included identifying the variable “subject” as the variable that represents the clusters.

Secondary analysis will be performed to compare: the secondary outcomes of retention and fracture of PPCs; PI, GI, and DI on the crowned tooth and the two adjacent teeth; presence or absence of a restoration with a dental material of the antagonist tooth; and wear of the antagonist tooth between treatment (ZC) and control (SSC) groups.

Both the ITT and secondary analyses will be performed within a 2-year period at 6, 12, 18, and 24 months. Repeated measures analysis (mixed model approaches) will be performed, and the principal independent variables will be treatment and time. The alpha level will be equal to 5%. All analyses will be performed with SAS (version 9.4; Cary, NC, USA).

The intra- and inter-investigator agreements for primary and secondary outcomes will be assessed using weighted Cohen’s Kappa. After calibration, the evaluators (one per center) will be tested by repeated exercises on the Socrative website (https://socrative.com/) with clinical cases suggested in a random way on the e-calib model (http://zep01793.dent.med.uni-muenchen.de/moodle/). Different clinical pictures were assessed twice, 15 days later.

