## Objectives and hypotheses

The overall aim of this RCT is to investigate the effectiveness of a new esthetic therapeutic option (EZCrowns; Sprig Oral Health Technologies) for the management of dental caries or structural anomalies. More specifically, the primary objective of this RCT is to assess the success of ZCs in PMs in comparison with SSCs with a follow-up of 2 years. The control treatment will be SSCs since this is the standard crown option [2–4].

Due to the esthetic superiority of ZCs (being a natural dental color) in comparison with SSCs (being metallic), our working hypothesis is that the success rates are equivalent between the ZCs and SSCs, given the absence of any major failure defined by Innes et al. [3] as a composite criterion including clinical and radiographic criteria.

The secondary objectives are to evaluate the retention and fracture rates, the gingival condition (plaque index, gingival index and depth of the pocket of Löe and Silness [8]), the wear of antagonist teeth [9, 10], and parental and child satisfaction (using a Likert scale) [11] between the study groups during the same period.

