### Study outcomes

The primary outcome is the success of the treatment. Success will be defined by the absence of major failure. A composite measure of signs and symptoms leading to diagnosis of irreversible pulpitis or periradicular periodontitis will be used to define major failure. This composite measure includes one or more of the following: pain, pulp infection, dental abscess, and periradicular pathology visible on radiograph [3].

The secondary outcomes are parental and child satisfaction (size, form, and color), retention and fracture of the PPC (two dichotomized variables, yes/no), the gingival state near the PPC using the indices Löe and Silness to record plaque index (PI), gingival index (GI) and depth of the pocket (DI) on the crowned tooth and the two adjacent teeth [8].

Parental and child satisfaction will be evaluated on a five-point Likert scale [11]. The DI will be assessed by soft periodontal probing on the sulcus mesial, distal, vestibular and lingual areas of the teeth. Finally, the wear of the antagonist tooth will be recorded (0: absence of wear; 1: wear on only the cusp point; and 2: wear at least at the cusps) [9, 10]. The presence or absence of a restoration with a dental material of the antagonist tooth will be also recorded.

Primary and secondary outcomes will be assessed clinically and radiographically by independent evaluators, one per center, at different periods during the study (postintervention and every 6 months during a total follow-up of 2 years). To prevent information bias, the evaluators will not be the operators who applied the treatment.

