### Sample size

Table 2 shows the sample size calculation for success rates ranging from 95% to 97%, alpha equal to 5%, with 90% power and an equivalence margin between the study groups of 10%. This table illustrates that the effective sample size of 81 teeth per treatment group will provide a power of 90% to assess effectiveness equivalence between the treatment groups. These rates were based on the systematic review of Innes et al. [3]. This calculation was based on the formula (Z _0.95_ + Z _0.90_)^2^ [Ps (1 – Ps) + Pn (1 – Pn)] / (Ps – Pn – D)^2^ (see http://people.ucalgary.ca/~patten/blackwelder.html) [14].

**Table 2 Tab2:** Sample size calculation

Rate	Teeth	Total required
80	274	548
85	218	438
90	154	308
95	81	162
97	49	98

Note: Rate of the outcome for the study groups, power = 90%, alpha = 5%, equivalence margin = 10%

Additionally, when we consider a hazard ratio (HR) = 1, moderate intraclass correlation (ICC) = 0.05, the percentage of teeth in each study group of 50%, the probability of observing an event of 90%, and two one-sided test (TOST) Zα = 1.64, this sample size of 81 teeth provides 80% power to test the equivalence between the study groups for margins ranging from 0.7 to 0.9. This sample size was calculated as described in [15].

Furthermore, assuming a dropout around 20%, the total sample size necessary will be 101 children. This dropout value was based on the experience of the research team from previous RCTs conducted in France [16]. This sample size is higher than those of past RCTs assessing the effectiveness of esthetic PPCs, which included 11 to 60 teeth per treatment group [6, 7].

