The choice of assessment criteria for the primary outcome is based on the systematic review of Innes et al. [3]. Using the same composite criteria will allow this RCT to be included in a future meta-analysis to compare different PPCs; their choice is more appropriate than the US Public Health Service criteria that is used more for the assessment of dental fillings. The success rate of a restoration can be related to the survey rate (presence in the mouth) of the tooth after 2 years of follow-up. This has the advantage of being longer than the 6 or 12 months of follow-up used in other studies focusing on PPCs [6, 7]. Other aspects of the criteria are also important and guide the choice of the criteria for the secondary outcome. The success of a restoration also includes its retention and integrity, the health of surrounding structures, and the satisfaction of both patients and parents with the restoration.

The clinical procedure is carried out under optimal conditions. One of the main advantages is that, if a pulpotomy must be done on the two PMs of the tooth pair, it has to be done under rubber dam isolation. Furthermore, the two PMs must present similar decay in depth, but this is often the case in children.

With sustained poor oral health in most developed communities [25], and greater importance being given to esthetic factors, the results of the present RCT will inform clinicians regarding the selection of clinical treatment options for severe dental decay which affect most children. The results will help them explain to the parents the advantages and disadvantages of the two possible solutions. The results will allow for advancement in the recommendations, and will be beneficial for the patient, the practitioner, and the public healthcare system.

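### The equivalence claim has only an ITT analysis behind it, and the primary outcome contains no crown-level event, so teeth that never received or did not keep a zirconia crown can dilute a true difference

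*Protocol article*

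**What the plan says.** The hypothesis in Objectives and hypotheses is one of equivalence: "our working hypothesis is that the success rates are equivalent between the ZCs and SSCs". Sample size fixes "alpha equal to 5%, with 90% power and an equivalence margin between the study groups of 10" percentage points.

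Under Statistical analysis, the paragraph that sets out the equivalence model opens with "An intent-to-treat (ITT) analysis will be conducted". That section later sums up the programme as follows: "Both the ITT and secondary analyses will be performed within a 2-year period at 6, 12, 18, and 24 months". The secondary analyses concern other outcomes, not a second population. The article names no per-protocol or as-treated set and no sensitivity analysis for deviations.

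Under Study outcomes, "Success will be defined by the absence of major failure", and "This composite measure includes one or more of the following: pain, pulp infection, dental abscess, and periradicular pathology visible on radiograph". None of these components is an event of the crown itself. Crown events appear among the secondary outcomes, as "retention and fracture of the PPC (two dichotomized variables, yes/no").

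**The concern.** In a superiority trial, ITT tends to be conservative because deviations shrink the difference the sponsor hopes to show. In an equivalence trial the sponsor hopes to show a small difference, so the same shrinkage helps the claim.

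Two features of this plan make that relevant:

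- **Not receiving the crown.** The SSC is placed first and the ZC at a separate visit 1 to 2 weeks later. A tooth allocated to ZC may therefore go without its crown after the SSC has been placed. ITT still counts it as ZC.
- **Not keeping the crown.** A ZC that debonds or fractures without pain, infection, abscess or periradicular pathology leaves the tooth a primary success.

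What is at stake is the error rate of the main claim. A ZC that is truly worse by the full margin could be declared equivalent more often than the nominal level implies.

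**Working it through.** **Step 1. The plan's own figure.** Inputs from Sample size: success 95% in both groups, margin D = 0.10, Z for 0.95 = 1.645, Z for 0.90 = 1.282.

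n = (1.645 + 1.282)² × [0.95×0.05 + 0.95×0.05] / 0.10² = 8.564 × 0.095 / 0.01 = 81.4 per group. The article gives 81. With 20% dropout, 81 / 0.80 = 101.25; the article gives 101. Both reproduce, so this point does not rest on an arithmetic error.

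**Step 2. Dilution under ITT.** Let the true on-treatment difference equal the margin: SSC 95%, ZC 85%. Let a fraction f of ZC teeth carry SSC-like risk. The documents give no value for f; 10% to 30% is an assumed range.

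- ZC rate under ITT: p = 0.85(1 − f) + 0.95f
- ITT difference: d = 0.95 − p
- SE = √{[0.95×0.05 + p(1 − p)] / 81}, treating teeth as independent
- Chance of passing the lower limit: Φ[(0.10 − d)/SE − z], with z = 1.645 for a 90% interval and 1.960 for a 95% interval

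Example, f = 0.20: p = 0.87, d = 0.08, SE = √[(0.0475 + 0.1131)/81] = 0.0445. With z = 1.645, Φ(0.449 − 1.645) = 11.6%. With z = 1.960, Φ(0.449 − 1.960) = 6.5%.

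| f (assumed) | ITT difference | 90% interval | 95% interval |
|---|---|---|---|
| 0% | 10 points | 5.0% | 2.5% |
| 10% | 9 points | 7.7% | 4.1% |
| 20% | 8 points | 11.6% | 6.5% |
| 30% | 7 points | 17.0% | 10.2% |

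Both intervals are shown because the sample-size formula uses Z for 0.95, which corresponds to a 90% interval, while Statistical analysis plans a 95% interval.

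The table tests the lower limit only. Requiring the upper limit as well subtracts 1 − Φ[(0.10 + d)/SE − z]. For f = 0, 10, 20 and 30% this gives 4.6, 7.1, 10.8 and 15.8% with a 90% interval, and 1.5, 2.7, 4.7 and 7.7% with a 95% interval. The pattern is the same at a lower level.

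**Step 3. Crown events outside the composite.** This is a separate question from dilution. Assume 5% major failure in both arms, no SSC loss, and independent ZC loss or fracture at rate q. The primary outcome then shows a difference of 0. If success also required an intact, retained crown, the difference would be 0.95 − 0.95(1 − q) = 0.95q: 4.75, 9.5, 14.25 and 19.0 points for q = 5, 10, 15 and 20%. It passes 10 points once q exceeds 0.10/0.95 = 10.5%. The values of q are assumptions too.

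**The case against.** **Silence in a condensed article.** The article does not say that ITT is the only set, and a per-protocol definition could stand in an analysis plan or full protocol not shown. That is fair, and it keeps the point modest. Still, the article does choose an analysis set for its main claim, and the one it names is not conservative for equivalence.

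**The composite is a reasoned choice.** It follows the cited systematic review so that the trial can enter a future meta-analysis, and retention and fracture are recorded at each visit and compared between groups. This stands: the composite should remain primary.

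**A tempting stronger reading: the Discussion contradicts the primary outcome.** It says "The success of a restoration also includes its retention and integrity", and a reader might infer an inconsistency. The text does not support that. The sentence just before says that these other aspects guided the choice of the secondary outcome, so the passage explains why retention and integrity are secondary.

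**A second stronger reading: replaced crowns count as successes.** The documents do not mention replacement. That such a tooth would count as a success is only an inference from the composite.

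**Direction.** A lost or cracked crown may expose the tooth to pulp disease, which is a primary failure and widens the difference. Dilution is the usual direction, not a certain one.

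**Magnitude.** The calculation uses a difference in proportions, whereas the plan fits a shared-frailty Cox model reporting a hazard ratio with a 95% interval. It also gives deviating teeth SSC-like risk for the whole two years, although a crown lost in follow-up changes risk only afterwards. Both objections stand, so the figures indicate size only.

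**Conclusion.** The point holds in a limited form. The plan tests equivalence, names only ITT, and uses a primary composite with no crown-level event, so deviations can dilute a true difference.

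Its size rests on an assumed deviation rate, a true difference exactly at the margin, and 81 independent teeth per group. For 10–30% deviation, the lower-limit error rises from 5% to about 8–17% with a 90% interval and from 2.5% to about 4–10% with a 95% interval. A reader might infer that the error always exceeds the stated 5%. It does not: with a 95% interval and 10% deviation it stays below 5%. Each figure is nevertheless above the level with no deviation.

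This weakens the support for the main claim; it does not invalidate the trial.

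**What to change.** 1. Keep the composite as the primary outcome and ITT as an analysis set.
2. Pre-specify a per-protocol analysis of pairs in which both teeth received the assigned crown. Do not censor a tooth at crown loss or fracture: if such teeth are at higher pulp risk, censoring is informative and could itself favour equivalence.
3. Analyse the per-protocol set on the same effect measure and margin as the ITT analysis, and claim equivalence only if the two agree.
4. Add a sensitivity analysis that counts crown loss or fracture as failure. This addresses crowns that were placed but not kept, which the per-protocol set leaves in.

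Cost: one extra analysis set, one sensitivity analysis and a slightly harder bar for claiming equivalence. Retention and fracture are already recorded at each visit; the crown actually placed may need its own case report form field. No interim analysis is planned, so the change can be fixed before results are known.

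### The primary Cox model takes success, not major failure, as its outcome event, so its hazard ratio is largely insensitive to failures and can support equivalence despite a large deficit

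*Protocol article*

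**What the plan says.** All references are to the Protocol article.

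- **Study outcomes:** "Success will be defined by the absence of major failure". A tooth with pain, pulp infection, abscess or periradicular pathology on the radiograph has failed.
- **Statistical analysis:** equivalence is assessed by a multivariable Cox model with shared frailty, "including success as the dependent variable (primary outcome defined by the absence of major failure: no = 0, yes = 1". The HR and its 95% CI come from PHREG. The section names no censoring value, event time, time origin or equivalence margin.
- **Sample size, proportions:** "success rates ranging from 95% to 97%, alpha equal to 5%, with 90% power and an equivalence margin between the study groups of 10" per cent, from which "the effective sample size of 81 teeth per treatment group will provide a power of 90" per cent.
- **Sample size, Cox model:** "hazard ratio (HR) = 1, moderate intraclass correlation (ICC) = 0.05, the percentage of teeth in each study group of 50" per cent, "the probability of observing an event of 90" per cent and "two one-sided test (TOST) Zα = 1.64". These are said to give 80% power with 81 teeth for margins from 0.7 to 0.9. The scale of those margins is not given.
- **Follow-up visits:** outcomes are assessed at 6, 12, 18 and 24 months.

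**The concern.** A Cox model compares the rates at which the event occurs. Here the quantity of interest is major failure, which has a time at which it is found. Success is the state of a tooth to which nothing has happened, and it has no onset. If success is the event, nearly all events fall at the last visit. At that visit almost every tooth still under observation has the event in both arms, and teeth that failed earlier have already left the risk set. The model then compares how quickly the remaining healthy teeth reach the end of follow-up.

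The stake is a false claim of equivalence. An HR close to 1 with a narrow interval would look like agreement between the crowns while one of them fails several times as often.

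**Working it through.** **1. Which outcome do the sizing inputs fit?** Planned success is 95–97%, so planned failure is 3–5%. An event probability of 90% is near the first and far from the second.

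**2. Reproduce the stated sample sizes.**
- Proportions (the plan's formula, which begins "This calculation was based on the formula (Z _0.95_ + Z _0.90_)^2"): (1.645 + 1.282)² × [2 × 0.95 × 0.05] / 0.10² = 81.4, against 81 stated.
- Cox equivalence: the cited source is not at hand, so a standard form is assumed, N = (1.64 + 1.282)² / (margin² × 0.25 × event probability) × (1 + ICC). With margin 0.7 on the log-HR scale and event probability 0.90: 8.54 / (0.49 × 0.25 × 0.90) × 1.05 = 81.3, against 81. This match needs the 90%, the log-HR scale (HR 0.50 to 2.01) and 81 as the total number of teeth. Read as HR 0.7, power is 0 with 81 teeth and about 36% with 162.

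**3. What the HR becomes with success as the event.** Assume that failures leave the risk set at the visit where they are found, that they are spread evenly over the four visits, and that nobody drops out. All events then fall at 24 months, and with Breslow ties HR = (d₁/n₁)/(d₀/n₀), where n is the number at risk at 24 months and d the number of successes.
- If every failure is found before 24 months, d = n in both arms and HR = 1 exactly, however many failed.
- With 5% versus 20% failure, three quarters of failures have left by then. For zirconia (ZC), 0.80/(1 − 0.15) = 0.941. For stainless steel (SSC), 0.95/(1 − 0.0375) = 0.987. HR = 0.941/0.987 = 0.95.
- The failure HR for the same case is about ln(0.80)/ln(0.95) = 4.35.

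**4. Simulation under the same assumptions** (treatment only, no frailty or covariates, 81 pairs, SSC success 95%, 90% CI against the margin):

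| ZC success | HR, success as event | HR, failure as event | CI inside HR 0.7–1.43 | CI inside log-HR ±0.7 |
|---|---|---|---|---|
| 95% | 1.00 | 1.0 | 100% | 100% |
| 85% | 0.97 | 3.1 | 95% | 100% |
| 80% | 0.95 | about 4.4 | 84% (97% with 101 pairs) | 100% |
| 75% | 0.94 | 5.5 | 60% | 100% |
| 50% | 0.81 | 12.8 | 0.5% | 96% |
| 20% | 0.51 | 25 | 0% | 1% |

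At 85% the deficit equals the plan's 10-point margin, where an equivalence test should pass in at most about 5% of trials. Repeat runs of the 80% row with 81 pairs gave 80–84%.

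**5. What failure as the event leaves.** Expected failures are 162 × 0.05 = 8.1, or 7.7 after dividing by 1.05. SE(log HR) = 2/√7.7 = 0.72. The 90% CI at HR = 1 is exp(±1.645 × 0.72) = 0.31 to 3.27. Its half-width on the log scale, about 1.18, exceeds 0.7 and 0.9, so TOST power is about 0. For 80% power at log-HR 0.7, 8.54/(0.49 × 0.25) = about 70 failures are needed, which is about 1,400 teeth at 5% failure, or 1,470 with the design effect.

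**The case against.** **The coding may be a slip.** The parenthesis could be meant as major failure no = 0, yes = 1, and 0/1 labels do not by themselves fix which value PHREG treats as censored. That is possible, and censoring rules are commonly left to an analysis plan. That failures would be censored is therefore an inference. But the literal text names success, and the separately stated 90% agrees with it. The 90% does not equal 95–97% either, so it may be an independent input error. Even then it is wrong for failure, and one of the two passages must change.

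**A reader might infer that equivalence would be declared whatever the crowns do.** The documents do not support that.
- The margin has no stated scale. At HR 0.8 the half-width with equal crowns (1.645 × 0.161 = 0.265) already exceeds −ln 0.8 = 0.223, so equivalence is never declared.
- At HR 0.7 it is declared in about 35–64% of trials for 5% versus 30% failure and about 1% for 5% versus 50%. Even log-HR ±0.7 refuses it at 20% ZC success.
- These shares use 90% CIs. The plan reports 95% CIs. For 5% versus 20% with 81 pairs there are about 142 successes, SE = 2/√142 = 0.168, and |ln 0.95| + 1.96 × 0.168 = 0.38. That exceeds −ln 0.7 = 0.357, so a typical trial would miss HR 0.7, but it is well inside 0.7 on the log scale.

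**The pull towards 1 depends on the time scale.** If every tooth is given 24 months, the HR roughly follows the ratio of success rates (0.79 for 75% versus 95%). If exact dates run from each crown's own placement, with an assumed visit spread of SD 14 days, the HR is about 2 with equal crowns, because the ZC is placed 1 to 2 weeks later. This limits what can be said about direction. On none of these scales does the HR estimate the relative hazard of failure.

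**Conclusion.** The point holds in this form: as written, the primary Cox model has success as its event, and the 90% event probability fits that reading and not a 3–5% failure rate. With visit-based times, the HR hardly reflects failures. A 15-point deficit gives an HR of about 0.95. Equivalence would be declared in about 84–97% of trials against HR 0.7–1.43 and in all against log-HR ±0.7, the scale that reproduces the plan's 81 teeth and 80% power.

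These figures rest on failures leaving the risk set when found, an even spread over visits, Breslow ties, 90% CIs, no dropout, and a model without the planned frailty and covariates. With another time scale or margin, the distortion changes in size and can change direction. Because the primary conclusion rests on this model, the text should be corrected before analysis.

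**What to change.** 1. In Statistical analysis, define the event as first major failure (failure = 1). Run time from that crown's placement to the visit at which failure is found, and censor failure-free teeth at their last assessment.
2. In Sample size, correct the 90% event probability, and withdraw or restate the 80% Cox power claim.
3. Base the equivalence conclusion on the difference in success at 24 months, analysed with the pairing, against the stated 10-point margin, for which 81 teeth per group was sized. Report the Cox failure HR as supportive.

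The cost is the Cox power figure, which cannot be kept with about 8 expected failures. The changes are to text only. Visits, data collection and recruitment are unaffected.

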## Methods

### Trial design and blindness

In this multicenter split-mouth RCT, a PM and its contralateral tooth in the same arch will be randomly assigned to a specific crown treatment group, ZC or SSC (Fig. 2). We plan to screen 101 individuals to successfully recruit 81 patients (see Sample size section below). We decided to use the split-mouth design because each subject forms its own control, adjusting for potential confounders.

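### The primary Cox model puts at least seven coefficients and a frailty variance on about 8 expected failures, and does not say which visit's antagonist-restoration value it adjusts for

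*Protocol article*

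**What the plan says.** The Statistical analysis section of the protocol article specifies a multivariable Cox model with shared frailty by subject, with treatment group as the main term. It then lists the adjustment set: "This analysis will also include the potential confounders age, gender, type of tooth (i.e., first or second primary molar), pulpotomy", followed by "number of surfaces affected by the lesion, and presence or absence of a restoration with a dental material of the antagonist tooth".

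Antagonist restoration has three roles in that section:
- an example of a baseline characteristic to be compared between groups;
- a confounder in the primary model;
- a variable compared between zirconia (ZC) and stainless steel (SSC) crowns in the secondary analysis, where the list includes "presence or absence of a restoration with a dental material of the antagonist tooth; and wear of the antagonist tooth".

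The Study outcomes section mentions it directly after antagonist wear: "The presence or absence of a restoration with a dental material of the antagonist tooth will be also recorded". The Baseline visit section does not list it.

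On confounding, the Trial design and blindness section justifies the split-mouth layout because "each subject forms its own control, adjusting for potential confounders".

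The Sample size section works with "success rates ranging from 95% to 97%, alpha equal to 5%, with 90% power" and takes the number of teeth from the 95% row of Table 2: "effective sample size of 81 teeth per treatment group will provide a power of 90" (per cent).

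**The concern.** A crown that succeeds in 95% of teeth leaves few failures, and a Cox model learns only from failures. Six covariates and a frailty variance on that base can make the prespecified primary analysis fail to converge or return infinite coefficients. The team would then have to change the model after seeing the data.

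The stated reason for adjusting, confounding, cannot apply to variables that are the same for both teeth of a pair.

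The antagonist variable raises a separate question. If a value recorded after crown placement entered the model, the analysis would condition on something that could depend on treatment, and the comparison could be biased. The text does not say which value is used.

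**Working it through.** **Reproducing the plan's figure.** Inputs from the Sample size section: success 95% in both groups, margin 10 points, one-sided Z at 0.95, power 90%. The section's formula gives (1.645 + 1.282)² × (2 × 0.95 × 0.05) / 0.10² = 81.36, against 81 stated. With 20% dropout, 81 / 0.8 = 101.25, against 101 children stated. The stated figures reproduce apart from rounding.

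**Expected failures.** Teeth × (1 − success rate):
- 162 teeth at 95%: 162 × 0.05 = 8.1
- 162 teeth at 97%: 162 × 0.03 = 4.9
- 202 teeth (all 101 children evaluable) at 95%: 202 × 0.05 = 10.1

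**Parameters.** Treatment plus six covariates is seven coefficients if each covariate takes one degree of freedom. The frailty variance makes eight.

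| Expected failures | Per coefficient (7) | Per parameter (8) |
|---|---|---|
| 4.9 | 0.69 | 0.61 |
| 8.1 | 1.16 | 1.01 |
| 10.1 | 1.44 | 1.26 |

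Even at 20% failure (162 × 0.20 = 32.4) there would be only 32.4 / 7 = 4.6 failures per coefficient.

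**Which event is counted.** The Sample size section also gives a Cox-based power statement with a 90% event probability. That would mean 162 × 0.90 = 145.8 events, about 21 per coefficient, but 90% failure contradicts 95% success. Success is defined as the absence of major failure, so failures are taken as the events here.

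**Consequences for fitting.** Null simulations used 81 pairs, 5% failure, Cox without frailty and assumed covariate distributions:
- Some coefficient was non-estimable or diverged in 12.9%, 14% and about 19% of trials in three separate simulations, against about 2–3% with treatment only.
- The SD of the treatment log hazard ratio (HR) was 0.81 against 0.75 in one simulation and 0.81 against 0.77 in another, a rise of 8% and 5%.
- In the simulation with SDs of 0.81 and 0.75, the 95% range of the estimated HR (true value 1) was 0.19–5.46 against 0.24–4.20.

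**Imprecision without covariates.** SE(log HR) ≈ 2/√8.1 = 0.70, so the 95% CI around HR 1 is about 0.25 to 3.96 with treatment alone.

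**Covariates within a pair.** Age and gender belong to the child. Table 1 requires both molars to be of the same type. Pulpotomy is less clear. Statistical analysis describes it as a tooth-pair characteristic. The Intervention section has it done on the SSC tooth when needed, but on the ZC tooth only when indicated on both. Read literally, the two teeth can differ, and in one direction by arm.

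**The case against.** The strongest reply is that the covariates do little harm to the estimate that matters. In one simulation the treatment coefficient itself diverged in 3.5% of trials with seven coefficients against 2.6% with treatment only, and 95% CI coverage was 98.6% in both. Most of the diverging coefficients belonged to covariates. This stands: a reader might infer that the adjustment set is what makes the treatment effect unstable, but the calculations attribute most of the imprecision to few failures.

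Second, a reader might infer that the model is over-adjusted and that the randomized comparison is broken. The document does not support that. Statistical analysis also names antagonist restoration as a baseline characteristic, and adjusting for a baseline value does no such harm. Nor does the article state that the crown affects later restoration of the antagonist. What stands is that the role and timing of the variable are left open.

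Third, a variable that cannot confound may still be adjusted for. Prognostic adjustment is legitimate, and a shared-frailty model is not purely within-pair. That is a fair defence when failures are plentiful. With about one per parameter it is weak, and the plan's stated reason is confounding.

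Fourth, treating pulpotomy as pair-level and discarding it would be unsafe given the Intervention wording. This also stands.

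**Conclusion.** The concern holds in a limited form. At the plan's own design rates the primary model has about one expected failure per parameter (0.6 to 1.3), with a material risk of non-estimable or diverging coefficients (roughly 13–19% of simulated null trials against 2–3%) and a modest loss of precision in the treatment HR. Age, gender and tooth type use up scarce events without removing any within-child confounding. Antagonist restoration has three roles and no stated visit for the model. A follow-up value could bias the comparison; a baseline value would not.

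The count of 8 is an expectation from the design rates, not a figure the article states. The simulation figures rest on assumed covariates and omit the frailty term. It would be wrong to conclude that dropping covariates makes the HR precise: SE(log HR) stays near 0.70.

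**What to change.** - Make the primary model treatment and child only, as a paired or frailty analysis. Failures per coefficient rise from about 1.2 to about 8 (8.1 / 1), or from 1.0 to about 4 (8.1 / 2) per parameter if the frailty variance is counted.
- Drop age, gender and tooth type.
- Move baseline number of surfaces, baseline antagonist restoration and indicated pulpotomy to a sensitivity model.
- State that only the antagonist value recorded before crown placement may be a covariate and that follow-up values are outcomes only. Confirm that the case report form captures the baseline value, since the Baseline visit section does not list it.
- Reconcile the pulpotomy wording for the two teeth in the Intervention section with its description as a pair characteristic in Statistical analysis.

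The cost is protocol and analysis-plan wording and, if the form lacks it, one baseline field. The downside is that there is no covariate-adjusted headline HR.
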